### Cord Blood Specimens

Umbilical cord blood (3-5 ml) is routinely collected following hospital births to establish infant red blood cell antigens. Study participants provide informed consent to allow the researchers to access the unused portion of these blood specimens that would otherwise be discarded. These samples are stored at -80°C as a source of fetal DNA.

### Summary of Frequency and Duration of Follow-Up

All participants are asked to complete three questionnaires: at <24 weeks gestation, at 34-36 weeks gestation and at 4 months post-partum for the All Our Babies Cohort Study. Blood collections are completed between 18-22 weeks of pregnancy and between 28-32 weeks of pregnancy. Women are contacted at approximately two weeks after their estimated due date to determine the delivery date. It is anticipated that participants of the All Our Babies Cohort Study will be followed-up every two to three years to provide the opportunity for life course research on maternal, child and family outcomes.

### Methods of Protecting Against Sources of Bias

All women who receive prenatal viral serology phlebotomy by Calgary Laboratory Service and consent to be contacted by researchers are contacted via telephone. Should they meet the inclusion criteria, the women are invited to participate in the All Our Babies Cohort Study. This recruitment strategy minimizes selection bias due to self-referral or patient populations at specific clinical practices and enables a citywide and surrounding area sampling approach.

Questionnaire data is collected prospectively, eliminating the influence of birth outcome on responses and potential for differential recall bias. However, the repeat use of standardized scales may introduce a form of bias where women remember answering the questions before and past answers influence responses on subsequent questionnaires. We anticipate that misclassification errors in exposure data will not be an issue in the information collected and generated from this cohort due to well-spaced and timely use of questionnaires.

Blood collections are offered at both a permanent laboratory location and by mobile phlebotomists to ensure that women are able to provide the blood sample at a location and time that is comfortable and convenient. The mobile phlebotomist option enables evening and weekend blood collections so that work hours are not a constraint. The flexibility of the blood collection options minimizes participant loss due to inconvenience or personal schedule demands.

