## Methods/Design

### Objectives

The aims of the All Our Babies Cohort Study are

a) To investigate genetic components of preterm birth through comparisons of transcriptomic patterns at 18-22 weeks and 28-32 weeks of pregnancy between spontaneous preterm birth cases and term delivering controls,

b) To examine the association between environmental factors and preterm birth, including access to routine prenatal care and health services, maternal mental and psychosocial health during pregnancy, and;

c) To examine the relative impact of genes and environment on the risk of preterm birth by exploring the interactions between medical history, gene expression patterns and environmental variables.

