### Questionnaire Data Collection

Questionnaires were developed to address the objectives of the All Our Babies Cohort Study and included input from academics, stakeholders and decision makers. These questionnaires (available on request) assess demographics, pregnancy history, service utilization, nutrition and exercise practices, mental health, social support, lifestyle and life history, and breastfeeding experiences through questions designed for this study as well as the following validated instruments: Edinburgh Postnatal Depression Scale [35], Spielberger State Anxiety Scale [36], MOS Social Support Scale [37], Perceived Stress Scale [38], T-ACE Screen for alcohol consumption risk [39], Parenting Morale Index [40], the Parental Expectations Scale for parenting self-efficacy [41], and the MCH Feeding Scale (personal communication, [name], Feeding Problem Questionnaire 2003). The questionnaires were pilot tested prior to study commencement and revised for unclear wording. The questionnaires were designed using the Cardiff Teleform software suite (Cardiff Teleform, Version 10.1, 2007) which enables the conversion to electronic data upon completion of paper-based copies.

The first questionnaire is mailed out at study enrollment for completion before 24 weeks of gestation. Women are given reminder calls beginning at 20 weeks gestation or 3 weeks after the questionnaire is mailed, whichever is later, to answer participants' questions and encourage completion and return of the questionnaire.

The second questionnaire is mailed to all participants at 32 weeks gestation, to be completed between 34-36 weeks gestation. At 36 weeks gestation, women are contacted by telephone to provide a reminder about the questionnaire. A modified version of this questionnaire is used for women who delivered prior to receiving or completing the questionnaire.

The third questionnaire is designed for completion at four months post-partum. Women are contacted two weeks after their expected due date to determine the birthdate of their infant(s). The questionnaire is mailed to participants at 3.5 months postpartum.

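### The claim that prospective questionnaires eliminate outcome influence does not hold for the second questionnaire, which women who deliver early answer after the birth on a modified form

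*Protocol article*

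**What the plan says.** Under Methods of Protecting Against Sources of Bias, the protocol article makes two assurances about the questionnaires. The first is "Questionnaire data is collected prospectively, eliminating the influence of birth outcome on responses and potential for differential recall bias". The second is "We anticipate that misclassification errors in exposure data will not be an issue in the information collected and generated from this cohort", which it attributes to the spacing and timeliness of the questionnaires. The only questionnaire bias it concedes is that women may remember earlier answers when a scale is repeated.

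Questionnaire Data Collection describes three waves:

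- First: "The first questionnaire is mailed out at study enrollment for completion before 24 weeks of gestation".
- Second: "The second questionnaire is mailed to all participants at 32 weeks gestation, to be completed between 34-36 weeks gestation". A reminder follows: "At 36 weeks gestation, women are contacted by telephone to provide a reminder about the questionnaire". The exception is stated directly: "A modified version of this questionnaire is used for women who delivered prior to receiving or completing the questionnaire".
- Third: "The third questionnaire is designed for completion at four months post-partum".

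Aim (b) under Objectives is "To examine the association between environmental factors and preterm birth", and it names mothers' mental and psychosocial health in pregnancy among those factors. Aim (c) builds on the same environmental variables. The follow-up summary gives 34-36 weeks as the time of the second questionnaire for all participants and does not repeat the exception.

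**The concern.** A prospective exposure is one recorded before the outcome is known. For the second questionnaire, that condition fails for women who deliver before they fill it in, and early delivery is the outcome under study. These women answer later relative to the birth, on a different form, knowing how the pregnancy ended. Most women who deliver at term can answer the standard form while still pregnant.

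The instruments include scales for anxiety, stress, depression and social support. A current-state measure taken after a preterm birth may partly describe a reaction to that birth. If such answers entered aims (b) or (c) as prenatal exposures, a consequence of preterm birth could be taken for a risk factor. An analyst who relied on the bias section would see no reason to separate them, because it declares all questionnaire data free of this problem.

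**Working it through.** The article gives no figure for this point, so the check sets the timings side by side and then sizes the affected group.

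**Inputs.** Preterm means birth before 37 completed weeks (Background). Births at 34-36 weeks make up 75% of preterm infants (Background). Sample Size expects about 180 preterm births among 1800 women, quotes a preterm rate of 9.1%, and plans about 25 of 80 spontaneous preterm array cases before 32 weeks.

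**Step 1: position of the second questionnaire relative to delivery.**

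| Delivery | State of the second questionnaire at birth | Form answered, if any |
|---|---|---|
| Before 32 weeks | Not yet mailed | Modified, after birth |
| 32-33 weeks | Mailed, completion window not open | Modified, unless returned early |
| 34-36 weeks | Completion window open | Either |
| 37 weeks or later | Window passed | Mostly standard, in pregnancy; modified for a few late responders |

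The first two rows contain only preterm births. The last row contains only term births. Form and timing are therefore strongly related to the outcome.

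**Step 2: births before 34 weeks.** The share is 1 - 0.75 = 25%.

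- With the stated 180 preterm births: 180 x 0.25 = 45.
- With the quoted rate: 1800 x 0.091 = 164 (rounded from 163.8), and 163.8 x 0.25 = 41.

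The quoted rate applied to 1800 does not return the stated 180, but the conclusion is the same with either count.

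**Step 3: births at 34-36 weeks.** Let q be the fraction of these women who have not completed the form when they deliver. The article does not give q, so it is varied as an assumption. With 180 x 0.75 = 135 such births, the number affected is 45 + 135q:

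- q = 0: 45 of 180 (25%)
- q = 0.25: 79 of 180 (44%)
- q = 0.5: 113 of 180 (63%)
- q = 1: 180 of 180 (100%)

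These counts treat all births before 34 weeks as affected and assume that every woman responds. Early returns at 32-33 weeks or non-response would lower them somewhat.

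**Step 4: planned array cases.** About 25/80 = 31% deliver before the second questionnaire is mailed. This percentage has a different base from the 25% in Step 2 (selected spontaneous cases, as against all preterm births), so the two should not be combined. It does show that for nearly a third of the cases meant for the gene-environment work, a standard second questionnaire cannot exist.

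**The case against.** Several objections have force.

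- **Not all preterm mothers are affected.** A reader might infer that every preterm mother answers after delivery. The article does not say so. The modified form goes only to women who delivered before receiving or completing the standard one. Many who deliver at 34-36 weeks may have answered first, a few at 32-33 weeks may have returned it early, and a late term responder may also receive the modified form. This stands.
- **Direction and size are unknown.** A reader might infer a bias away from the null. For illustration, assume a true 20% prevalence of high anxiety in both groups (odds 0.25), raised by 10 to 20 points when asked after a preterm birth. If 25% of preterm women are affected, the case prevalence is 22.5% to 25%, and the odds ratio is 1.16 to 1.33. If all are affected, the prevalence is 30% to 40%, and the odds ratio is 1.71 to 2.67. The arithmetic is right, but neither the prevalence nor the shift has a source in the documents. The content of the modified form is not shown either: it may omit current-state scales or ask only about the time before delivery. Reported support or service use could move either way. This stands too.
- **No stated analysis commits the error.** The Statistical Analysis section is general, and which wave supplies the exposures may be settled in a fuller document. This stands only in part. The point does not rest on missing detail: the article makes a positive, unqualified claim that its own data collection contradicts.
- **The main design is untouched.** Sample size and case selection rest on the transcriptomic comparison. That is true, but aims (b) and (c) are also stated aims.

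**Conclusion.** The contradiction is established from the text alone. The bias section claims a protection that the second questionnaire does not have, and the assurance on exposure misclassification is unsupported for the same reason. The claim is sound for the first questionnaire, which is due before 24 weeks and so precedes nearly all preterm births.

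At least about a quarter of preterm births are involved, roughly 45 of 180 or 41 of 164, subject to a few early returns and to response. How many more depends on the unreported share of women delivering at 34-36 weeks who had not yet answered.

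Two stronger conclusions are not supported. The article does not show that a spurious association will arise, or in which direction. Nor are the comparisons at four months postpartum, listed in part (b) of Proposed Outcome Measures, compromised: they are post-delivery by design in both groups, and any effect of the birth is part of what they compare.

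**What to change.** 1. In the bias section, limit the claim to the first questionnaire. State that in the second questionnaire timing and form differ by outcome, and qualify the misclassification assurance accordingly.
2. For associations with preterm birth in aims (b) and (c), take primary exposures from first questionnaires completed before delivery.
3. Exclude modified post-delivery forms from risk-factor analyses, or use them only in a sensitivity analysis by form version and timing.
4. If second-questionnaire exposures from pre-delivery forms are used, compare only women still pregnant when the form was completed. A time-to-delivery model with entry at the completion date is one way to do this, but it is not required.

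**Cost.** The change is to wording and analysis rules, with no new data collection. Form version already marks the known post-delivery answers. Steps 2 and 4 also need completion dates, and the article does not say whether these are recorded. The price is that exposures asked only in the third trimester cannot be related to births before about 34 weeks.

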### Proposed Outcome Measures

a) Transcriptomic profiles from maternal blood samples collected at 18-22 weeks and 28-32 weeks of pregnancy will be compared between two groups (women who deliver at term and women who deliver preterm) for patterns predictive of preterm birth.

b) Health service utilization, maternal social support, psychosocial well-being, mental health, breastfeeding and parenting support at four months postpartum will be compared between term and preterm deliveries.

c) The relative contribution of the environmental risk and the genetic risk will be compared between term and preterm deliveries.

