The pathophysiology of preterm birth is complex due to multi-factorial causes and its heterogeneous nature. Preterm birth is often categorized as (1) iatrogenic when delivery is a consequence of medical intervention (30-35%); (2) spontaneous when it occurs after spontaneous labour with intact membranes (40-45%); or (3) the result of preterm premature rupture of the membranes (PPROM) (25-30%) [3]. While gestational diabetes, preeclampsia and intrauterine growth restriction have all been associated with iatrogenic preterm birth, the underlying causes of spontaneous preterm birth are less clear. Reported risk factors are widespread and diverse, supporting the hypothesis of gene-gene and gene-environment interactions in the pathophysiology of spontaneous preterm birth. Highly associated risk factors include a previous preterm birth or a relative with preterm birth [10] or a black racial background [11], suggesting genetic causes. Other demographic factors such as low socioeconomic status [12] and maternal stress [13] have shown an association, indicating that the environment contributes to the etiology of spontaneous preterm birth.

Evidence for a causal role of infection and inflammation in preterm birth has been reviewed in detail [14]. Both interleukin (IL)-1β and tumor necrosis factor (TNF)α are cytokines produced by the intrauterine tissues in response to bacterial infections [15,16] which stimulate prostaglandin synthesis [17] and increase uterine contractility. Several groups have investigated the relationship between a single nucleotide polymorphism (SNP) located in the promoter of the TNFα gene (G-308>A) (referred to as the TNF-2 allele) and preterm birth, but inconsistent results have been reported [18-21]. A recent meta-analysis of seven studies [22] found no association between preterm parturition and the TNF-2 allele. Similarly, studies examining polymorphisms in IL-1β and IL-6 as well as other variants have also produced inconsistent results [19,23,24].

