### Maternal Blood Specimens

Maternal blood samples are collected at 18-22 weeks gestation and at 28-32 weeks gestation either at a laboratory location or by a mobile phlebotomist. Participants are contacted at 17 and 27 weeks gestation by telephone and/or email to begin scheduling their first and second blood collections respectively. Collections can occur at any time of day and fasting is not required.

Four PAXgene™ blood RNA tubes (PreAnalytix/BD Canada, Mississauga, Ontario, Canada) are used at each blood collection. These tubes are specially designed to preserve RNA in whole blood at the time of collection. Blood is also collected into a heparin tube to isolate plasma (first collection), a serum collection tube (second collection) and into an EDTA tube for maternal DNA extraction.

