#### Statistical Analysis

Transcriptomic data, medical record data and self-report questionnaire data will first be analyzed univariately. Participant characteristics will be assessed and compared to the pregnant and parenting population in the province of Alberta and nationwide across Canada. Should transcriptomic signatures predictive of preterm delivery phenotypes be elucidated from the microarray analyses and validation, gene-environment interactions will be explored by integrating the transcriptomic data with the questionnaire and medical record datasets using appropriate statistical analytical techniques.

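### Outcome (c) and aim (a) label gene expression as genetic risk, so the planned comparison cannot be read as genes versus environment

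*Protocol article*

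**What the plan says.** Three statements in the protocol article define the genetic side of the study.

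- Objectives, aim (a): "To investigate genetic components of preterm birth through comparisons of transcriptomic patterns at 18-22 weeks and 28-32 weeks of pregnancy", contrasting spontaneous preterm cases with term controls.
- Objectives, aim (c), reads: "To examine the relative impact of genes and environment on the risk of preterm birth by exploring the interactions between medical history, gene expression patterns", together with environmental variables.
- Proposed Outcome Measures, item (c): "The relative contribution of the environmental risk and the genetic risk will be compared between term and preterm deliveries".

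The data behind them are described as follows.

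- Transcriptomic Analysis divides the extracted RNA into three aliquots: quality assessment, microarray, and validation by real-time PCR. All three uses are on RNA.
- Statistical Analysis names transcriptomic, medical record and questionnaire data. If predictive signatures emerge, "gene-environment interactions will be explored by integrating the transcriptomic data with the questionnaire and medical record datasets". Expression is the gene term.
- Maternal Blood Specimens has blood drawn "into an EDTA tube for maternal DNA extraction", and Cord Blood Specimens stores cord blood as a fetal DNA source. No section describes genotyping or any other analysis of that DNA. Recruitment Strategies and the section on obstetrical and birth records mention genetic analyses, but the only ones described are the RNA arrays.

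**The concern.** The Background builds the case for genetic risk on inherited quantities: single nucleotide polymorphisms, a personal or family history of preterm birth, racial background, and a reported interaction between an allele and bacterial vaginosis. An allele is fixed before any exposure in pregnancy. A transcript level at 18-22 or 28-32 weeks is not. It may reflect infection, inflammation or stress, all of which the Background names as contributors to preterm birth.

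If expression stands in for genes in outcome (c), the comparison sets one possible consequence of environment against environment itself. A transcript raised by an exposure would be counted as genetic, and a reader of the result could conclude that risk is inherited when the data cannot show that. At stake is the interpretation of one stated outcome and of the gene-environment analysis built on it.

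**Working it through.** No figure in the article is being reproduced here. The check compares the sections and then illustrates the mechanism with assumed effects.

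**1. Is anything other than expression available for the gene term?** Going through the molecular sections in turn: the array sample is 80 cases and 80 controls at two time points (Sample Size: 160 × 2 = 320 arrays); the assays are all on RNA; the analysis section lists no genotype data; DNA is collected without a described use. As the article stands, the genetic risk in outcome (c) is expression.

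**2. Can expression be downstream of environment?** The Background describes interleukin-1β and TNFα as "cytokines produced by the intrauterine tissues in response to bacterial infections". That concerns intrauterine tissue, not maternal leukocytes, so it shows that gene products respond to exposure without measuring how far blood RNA does. Cases and controls are loosely matched on age, body mass index and smoking only. Stress, infection and socioeconomic status remain free to differ between the groups.

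**3. What follows if environment acts through expression?** Let E be an environmental score and X expression, both standardised with correlation r. Let the log-odds of preterm birth be b_X·X + b_E·E, with no genotype effect. Then approximately:

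- OR for E alone = exp(b_E + r·b_X)
- OR for E with X in the model = exp(b_E)

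The values of r, b_X and b_E are assumptions; none comes from the article. Take b_X = 0.7, so the expression OR is exp(0.7) ≈ 2.0. The simulated odds ratios lie slightly below the approximation because the odds ratio is not collapsible.

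| b_E | r | E alone, formula | E alone, simulated | E jointly, formula |
|---|---|---|---|---|
| 0 | 0.3 | exp(0.21) = 1.23 | 1.22-1.23 | 1.00 |
| 0 | 0.5 | exp(0.35) = 1.42 | 1.40 | 1.00 |
| 0 | 0.6 | exp(0.42) = 1.52 | 1.50-1.52 | 1.00 |
| 0 | 0.7 | exp(0.49) = 1.63 | 1.62 | 1.00 |
| 0.3 | 0.3 | exp(0.51) = 1.67 | about 1.63 | 1.35 |
| 0.3 | 0.6 | exp(0.72) = 2.05 | about 2.0 | 1.35 |

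The simulated joint values agree to within about 0.01. The share of environment's total log-odds that leaves the environmental term is r·b_X / (b_E + r·b_X). It is 100% in the b_E = 0 rows by construction, 0.21/0.51 = 41% in the fifth row and 0.42/0.72 = 58% in the last.

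**4. What if environment only confounds?** Suppose environment drives both expression and preterm birth (log-odds 0.7), and expression has no effect. The expression OR alone is then 1.22, 1.41 and 1.62 at r = 0.3, 0.5 and 0.7. It returns to about 1.0 once the exposure is measured and adjusted for, while the environmental OR stays near 2.0. In that structure a joint model does not understate environment. An unmeasured exposure could not be adjusted for in this way.

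**5. Where the problem does not reach.** Aim (b) examines environmental factors and preterm birth separately from expression. The cohort-wide comparisons use 1800 women, whereas arrays exist for only 160, so expression cannot be a term in those regressions.

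**The case against.** The strongest reply is that this is a matter of wording. Aim (c) says openly that expression patterns are the measure, so readers are not misled about the data. No joint model is specified: the gene-environment work is exploratory, conditional on finding a signature, and left to suitable techniques that the full protocol or analysis plan may define. Aim (b) already gives environmental effects without expression. DNA is collected and written consent covers genetic analyses, so a condensed article may simply omit a genotype analysis.

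Much of this stands. Aim (a) weighs nothing against environment; only its label is at fault. The service and policy uses under Significance of The Study rest mainly on questionnaire and record data. Smoking, one route from environment to expression, is partly balanced by the matching.

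A reader might infer that the plan would report essentially all risk as genetic, or that the study will understate environment throughout. The document supports neither. The first follows only from assuming that environment acts wholly through expression; the second overlooks aim (b) and the absence of a specified model.

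The reply does not remove the construct problem. Outcome (c) promises a relative contribution of genetic risk, and no technique applied to expression data alone recovers inherited risk. That promise sits in the stated aims and outcomes, so it is not a detail deferred to an analysis plan.

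**Conclusion.** The point holds as a construct error in outcome (c) and in the labels of aims (a) and (c). A comparison of expression with environment cannot be read as genes versus environment. Where environment acts through expression, any model containing both understates environment's total effect. In the illustrations with a direct environmental effect, the odds ratio falls from about 1.63 to 1.35 or from about 2.0 to 1.35. The size rests entirely on the assumed mediation, and pure confounding by a measured exposure produces no such loss. The conclusion also assumes that no DNA analysis is planned beyond what the article describes. Prediction of preterm birth from expression and the cohort-wide environmental analyses are unaffected. It should be corrected because it changes what the study may conclude.

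**What to change.** - Replace the references to genetic components in aim (a), genes in aim (c) and genetic risk in outcome (c) with gene expression.
- Define outcome (c) as the incremental prediction of preterm birth from expression over environmental factors and medical history.
- Report it beside the environmental effects from aim (b), estimated without conditioning on expression.
- Make no genes-versus-environment attribution unless the collected DNA is analysed.

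The cost is rewording two aims and one outcome measure and stating one nested model comparison; no new assays are needed. The downside is that the study gives up a headline claim, but one that its described data cannot support.
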